## Abstract

**Introduction::**

Mild subclinical hypothyroidism (SCH) can cause depression, fatigue, cognitive dysfunction, or other hypothyroid symptoms, and even progress to hypothyroidism. The treatment of mild SCH is controversial. Shuganjianpihuatanxingqi decoction (SD) is a frequently prescribed Chinese herbal medicine in patients with mild SCH. However, scientific evidence is needed to confirm the therapeutic effect of SD.

**Methods and analysis::**

This study is a randomized, double-blind, and controlled clinical trial. A total of 228 participants with the diagnosis of mild SCH will be randomly assigned to the SD or placebo group in a ratio of 1:1. Participants will receive treatment for 12 weeks and undergo 12-month follow-up. The primary outcome measure is the thyroid-stimulating hormone level, and secondary outcomes will be the differences in the results of Thyroid-related Quality of Life Questionnaire, blood lipids, and Traditional Chinese Medicine Symptom Score Scale between baseline and at 12 weeks after intervention.

**Ethics and dissemination::**

The study has been approved by Guang’anmen Hospital of China Academy of Chinese Medical Sciences (no.2018-005-ky-01). The trial results will be published via peer-reviewed journals and the Clinical Research Information Service.

**Trial registration number::**

ChiCTR1800015781 (approval date: 20 April 2018).

## Introduction

1

Hypothyroidism is a common disease of thyroid hormone deficiency. In adults, the most common symptoms of hypothyroidism include fatigue, lethargy, constipation, cold intolerance, weight gain, sound changes, and dry skin. In severe cases, the absence of treatment can result in mortality.^[1]^ Subclinical hypothyroidism (SCH) is a condition of elevated serum thyroid stimulating hormone (TSH) with normal serum free thyroxine (fT4).^[2]^ Studies have indicated a high prevalence rate of SCH in the United States, ranging from 3% to 18% in the adult population, with higher rates among women and the elderly.^[3,4]^ Another study showed that the prevalence rate of untreated SCH in Spain was 4.6%.^[5]^ A cross-sectional study of 10 cities in China reported that the number of patients with SCH increased from 3.22% to 16.7% in the past decade.^[6]^ Patients with SCH are more prone to depressive symptoms, decreased quality of life, cognitive function, and memory loss than those with normal thyroid function.^[7–9]^ In addition, thyroid hormones have a variety of complex effects on the heart, blood vessels, bone, and brain.^[10]^ Patients with SCH show a higher risk of hyperlipidemia, atherosclerosis, hypothyroidism symptoms, and cardiovascular events.^[11,12]^ The treatment of SCH remains controversial.^[13]^ In general, a thyrotropin cutoff level of 10 mIU/L is used to distinguish between mild and more severe SCH.^[14,15]^ While most experts recommend levothyroxine therapy in patients with SCH with TSH level of greater than 10 mIU/L, there is lack of consensus on whether patients with mild SCH with TSH levels less than 10 mIU/L should be treated.^[16]^ A Cochrane systematic review showed that levothyroxine replacement therapy in patients with SCH did not improve survival or reduce cardiovascular morbidity. Data on health-related quality of life and symptoms showed no significant differences between the intervention groups.^[17]^ Excessive levothyroxine intervention may cause SCH.^[16]^ Therefore, most patients with mild SCH are recommended for follow-up observation. However, patients often complain of depression, fatigue, cognitive function, or other hypothyroid symptoms. In addition, under increasing health awareness among patients, mild SCH that has not been treated tends to aggravate the patients’ anxiety and depression. As a result, many patients seek Chinese herbal medicine for treatment; in addition, attempts have been made to provide Chinese medicine treatment in patients with mild SCH.

Chinese medicine has a long history of treatment in patients with thyroid disease. Over a period of thousands of years, Chinese medicine has accumulated rich experience and numerous drugs to target thyroid disease. In the third century BC, TCM doctors recorded some typical symptoms of thyroid dysfunction and named the disease Ying disease. In the Sui dynasty, a Chinese medicine book, the *Zhu Bing Yuan Hou Lun* indicated that thyroid disease is related to regional factors and the patients’ mental state. In the Tang Dynasty, iodine-containing herbal Chinese medicine was used to treat patients with iodine-deficient goiter. Currently, traditional Chinese medicine (TCM) is widely used to treat patients with thyroid diseases in China. Some preliminary studies reported the therapeutic effects of TCM in patients with thyroid diseases. A clinical study reported that Chinese medicine can reduce the size of goiter in patients with multinodular and diffuse goiter.^[18]^ A randomized trial reported that a Chinese herbal dispersion formula improved the treatment outcomes of antithyroid drug treatment in patients with hyperthyroidism with neurologic manifestations of Graves’ disease by means of modulating the levels of IL-2, IL-8, and IL-17.^[19]^*Prunella vulgaris L.* promoted apoptosis of well-differentiated human thyroid carcinoma cells.^[20]^ Prunellae oral liquid can be used as an adjunct treatment in patients with goiter.^[21]^ A case report revealed potential effectiveness of Anemarrhena Bunge decoction in patients with Graves’ disease with resistance to meilizazole.^[22]^ In the treatment of hypothyroidism, Chinese herbal medicine has been used alone or in combination with levothyroxine therapy to relieve the symptoms of patients’ discomfort.^[23,24]^

SD, a formula comprised of multiple herbs, such as, *Pinellia ternata (Thunb.) Breit.*, *Magnolia officinalis Rehd. et Wils* and *Prunella vulgaris L*., and so on is a frequently prescribed TCM in patients with mild SCH. Based on TCM theory, it can improve the symptoms of depression, fatigue, and hypothyroidism. SD evolved on the basis of the Banxia-houpu decoction. *Jin Gui Yao Lue* by the reputed TCM doctor Zhang Zhongjing of the Han Dynasty stated that a Banxia-houpu decoction could be used to improve depression and throat discomfort. An in vivo study reported that Banxia-houpu decoction can increase the anti-stress effect through the hypothalamus-pituitary-adrenal gland axis and modification of stress behaviors.^[25]^ Water extract of *Magnolia officinalis Rehd. et Wils* has antidepressant-like effects by improving the hypothalamus-pituitary-adrenal axis function, promoting expression of brain-derived neurotrophic factor in the hippocampus, and increasing hippocampal neurogenesis.^[26]^ Autoimmune thyroiditis is the most common endogenous cause of SCH.^[27]^ The active ingredients of *Magnolia officinalis Rehd. et Wils* can strengthen innate immune signaling responses and modulate inflammation^[28,29]^; whereas, the active ingredients of *Poria cocos (Schw.) Wolf* can regulate mammalian immune cells, with potential for use in treating Th2-mediated immune disorders.^[30]^

In a preliminary study including a small sample, SD showed effect to improve symptoms in patients with mild SCH and reduce TSH levels; however, there have been a few high-quality trials and more evidence is needed to prove the therapeutic effect of SD. This study aims to evaluate the effectiveness and safety of SD in patients with mild SCH using strict high-quality methodology per Consolidated Standards of Reporting Trails (CONSORT) statement for randomized controlled trials of herbal medicine.^[31]^

The results of this trial will hopefully provide clinical evidence for the treatment of patients with mild SCH.

## Methods

2

### Objectives

2.1

The aim of this trial is to assess the efficacy and safety of SD in patients with mild SCH.

### Study design

2.2

This is a double-blind, randomized, and controlled trial to investigate the efficacy and safety of SD compared with that of the placebo. The study will be conducted in 3 centers in China: Guang’anmen Hospital of China Academy of Chinese Medical Sciences, Xiyuan Hospital of China Academy of Chinese Medical Sciences, and Wangjing Hospital of China Academy of Chinese Medical Sciences. Patients with mild SCH will undergo a standardized baseline evaluation before treatment including detailed history taking, physical examination, and laboratory testing. Included participants will be randomly divided into two groups, an SD group and the other that will receive placebo. The efficacy and safety of SD will be assessed after 12 weeks’ treatment and 12 months’ follow-up at drug withdrawal. All visits will be recorded in Care Report Forms (CRFs). The flow-chart is shown in Figure 1, and the time-point of assessment is shown in Table 1. The development of the protocol of this study is per Standard Protocol Items: Recommendations for Interventional Trials (SPIRIT) guideline.^[32]^

**Figure 1 F1:**
[figure not shown]
Flow diagram. SD = Shuganjianpihuatanxingqi decoction.

**Table 1 T1:**
[figure not shown]
Schedule of enrollment, intervention, and assessment.

### Study setting and recruitment

2.3

Between December 2018 and December 2020, a total of 228 patients will be recruited in the three centers mentioned above through posters, hospitals’ website, and networks. The research assistants will manage the recruitment, and the endocrinologists will diagnose the participants.

### Participants

2.4

#### Diagnosis criteria

2.4.1

The diagnostic criteria for mild SCH are based on the criteria set by the American Association of Clinical Endocrinologists and the American Thyroid Association in 2012.^[33]^

#### Inclusion criteria

2.4.2

1.Diagnosis based on persistently elevated TSH levels (4.6–10.0 mU/L), with fT4 within the reference range.2.Age of minimum of 18 years to a maximum of 70 years.3.Capability of complete compliance and completion of follow-up.4.Willingness to provide written informed consent.

#### Exclusion criteria

2.4.3

1.Current prescription of levothyroxine, antithyroid drugs, amiodarone, or lithium.2.Recent thyroid surgery or radioiodine therapy within 1-year of the study's start date.3.History or presence of clinically relevant cardiovascular, renal, metabolic, hematological, neurological, psychiatric, systemic, or infectious disease or malignant tumor.4.Severe mental disorder.5.Recent hospitalization for major illness or elective surgery within 1-year of the study's start date.6.Pregnancy or lactation, intention to become pregnant, and/or not using appropriate contraceptive methods.7.Allergy to components of the agents used in the study.8.Terminal illness.9.Genetic problems such as galactose intolerance, Lapp lactose deficiency, or glucose-galactose malabsorption.10.History of alcoholism or substance abuse.11.Recent participation in other clinical trials.

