#### Secondary outcomes

2.8.2

The secondary endpoint is the change in TSH from baseline to week 12. Biochemical measurements of TSH levels will be performed in the laboratory of each center at 4 weeks’ interval. In addition, the change in blood lipids, including the total cholesterol, triglyceride, high-density lipoprotein will be measured.

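### The one-year look-backs in exclusions 2 and 5 run from the study's start rather than from each participant's screening, so they stop working as recruitment proceeds (minor)

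*Protocol article*

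**What the plan says.** Two exclusions in section 2.4.3 of the protocol article carry a one-year limit:

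- Exclusion 2: "Recent thyroid surgery or radioiodine therapy within 1-year of the study's start date".
- Exclusion 5: "Recent hospitalization for major illness or elective surgery within 1-year of the study's start date".

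Section 2.3 gives the recruitment period: "Between December 2018 and December 2020, a total of 228 patients will be recruited". The article states no separate study start date and nowhere defines that date as a participant's own screening, consent or randomisation.

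Three other criteria bear on the same patients:

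- Inclusion 1 (section 2.4.2): "Diagnosis based on persistently elevated TSH levels (4.6–10.0 mU/L), with fT4 within the reference range". No retest interval or number of tests is printed.
- Exclusion 1: "Current prescription of levothyroxine, antithyroid drugs, amiodarone, or lithium".
- Exclusion 3: "History or presence of clinically relevant cardiovascular, renal, metabolic, hematological, neurological, psychiatric, systemic, or infectious disease or malignant tumor". It names neither thyroid surgery nor radioiodine.

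TSH is an efficacy outcome wherever it is placed. The Abstract says "The primary outcome measure is the thyroid-stimulating hormone level", while section 2.8.2 says "The secondary endpoint is the change in TSH from baseline to week 12".

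**The concern.** Both exclusions open with the word 'recent', which has meaning only relative to the person being screened. Their presumable purpose is to keep out people whose TSH or symptoms may still be shifting after a procedure or an illness. A limit tied to one calendar date serves that purpose for those screened at the outset and progressively less for those screened later. Late in recruitment the literal rule can work backwards, letting in someone treated a few months ago and turning away someone treated almost three years ago.

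Two things are at stake. Some participants could enter with an unstable baseline on TSH or ThyPRO, which adds variance to the 12-week changes. Also, with three centres, a site that applies the printed words and a site that counts back from screening would apply different eligibility rules, and the article gives a monitor no basis for saying which is compliant.

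**Working it through.** The plan gives no figure to reproduce, so the check is calendar arithmetic.

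**Inputs**

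- Look-back of 12 months, anchored to the study start (section 2.4.3, exclusions 2 and 5).
- Recruitment from December 2018 to December 2020, taken as 24 months (section 2.3).
- Assumption: the study start is the start of recruitment, December 2018.
- Assumption: recruitment is uniform over the period.

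**Two example patients**

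- Radioiodine in June 2020, screened in November 2020. The treatment is 5 months before screening but 18 months after the study start. It lies outside a one-year window on either side of the start, so the patient is not excluded.
- Thyroid surgery in January 2018, screened in December 2020. The surgery is 35 months before screening but 11 months before the study start. It lies inside the window, so the patient is excluded.

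**Coverage of a participant's own look-back**

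For someone screened t months after the start, the relevant period is t − 12 to t. Compare it with the window that the text excludes.

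- Window before the start only, −12 to 0: uncovered months = min(t, 12).
- Window either side of the start, −12 to +12: uncovered months = max(0, t − 12).

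| Month screened | Uncovered of 12, before only | Uncovered of 12, either side |
|---|---|---|
| 0 | 0 | 0 |
| 6 | 6 | 0 |
| 12 | 12 | 0 |
| 18 | 12 | 6 |
| 24 | 12 | 12 |

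Averages over 24 months:

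- Before only: mean uncovered = (12 × 6 + 12 × 12)/24 = 216/24 = 9.0 months, so 3/12 = 25% is covered. The half screened after month 12 have no look-back at all.
- Either side: mean uncovered = (12 × 0 + 12 × 6)/24 = 72/24 = 3.0 months, so 9/12 = 75% is covered. The half screened after month 12 have some gap.

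**Sensitivity**

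- Counting December 2020 in full (25 months), mean uncovered time is (72 + 13 × 12)/25 = 9.12 months, or (72 + 1 × 12)/25 = 3.36 months. Coverage is 24% or 72%.
- If the study start were instead registration in April 2018 (section 2.9.5), 8 months before recruitment, coverage falls. Before only: (4 × ⅓ × ½)/24 ≈ 3%. Either side: (4 + 12 × ½)/24 ≈ 42%. Both example patients are classified as before.

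**After rewording**

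If the year is counted back from each participant's screening visit, uncovered time is 0 of 12 months for everyone, whenever screened.

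**The case against.** The strongest reply is that no experienced endocrinologist would read the rule literally. The word 'recent' signals the intention, the investigators are trained clinicians, two of them diagnose each case (section 2.6), and the lead hospital visits sites (section 2.9.3). The full protocol, which is not shown, may also fix the anchor. That lowers the chance that the literal rule is ever applied. It does not make the printed rule right: it names a specific date, and nothing in the article replaces it.

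The second reply is that other criteria already remove many of these patients. Inclusion 1 asks for TSH elevation that persists, exclusion 1 removes anyone on thyroid replacement after a procedure, and exclusion 3 removes malignancy and much major illness without a time limit. This stands in large part. What remains is mainly untreated patients with a recent procedure for benign thyroid disease and mild TSH elevation, and patients with recent elective surgery. No other criterion excludes them.

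A reader might infer three stronger things, none of which the documents support:

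- **That 25% or 75% measures impact on the trial.** These figures describe calendar time covered. The article gives no count of patients who would enter this way, and no effect on TSH or ThyPRO can be derived.
- **That the comparison between arms is biased.** Allocation is randomised 1:1 and blinded (sections 2.2 and 2.5), so such patients fall to either arm by chance.
- **That arms become unbalanced within centres.** Nothing in the article allows that to be calculated, and section 2.9.2 describes no centre-level comparison.

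**Conclusion.** The point holds as a wording defect of minor severity. Exclusions 2 and 5 state a rule with the wrong anchor, which is different from a detail left to a fuller document. Some gap exists on both readings of the one-year window, and for a participant screened 24 months after the start the uncovered part is the full 12 months on either. The averages of 25% and 75% rest on uniform recruitment and on December 2018 as the study start, which the article does not state. An earlier start would lower both.

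The number of patients affected is unknown and probably small. The expected consequence is some added variance, together with eligibility that drifts over calendar time and may differ between sites.

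**What to change.** In exclusions 2 and 5 of section 2.4.3, replace the reference to the study's start with the wording 'within 1 year before the participant's screening visit'. The length of the period stays as it is.

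The cost is one phrase in two criteria, made by amendment, with no added procedures. A few late-screened patients become ineligible, and some whose procedure or admission is more than a year old at screening become eligible.

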### Randomization, allocation concealment, and blinding

2.5

Participants will be randomly assigned to either the SD or placebo group in a 1:1 ratio. Randomization using Statistics Analysis System (SAS) software will be performed by independent staff statisticians. The randomization numbers are kept in opaque sealed envelopes.

Allocation concealment will be performed by the Data Management Center of Guang’anmen Hospital. Randomization code generation and drug blinding will be implemented independent of the data collection, evaluation, and analysis. The drug administrator at each participating medical center will enroll patients sequentially on the basis of screening order. Both participants and investigators will be blinded to the allocation until completion of the trial. To achieve blinding, the same kind of packaging will be used for both the drug and placebo in each group. The placebo will be matched to the corresponding medicine in terms of size, color, shape, taste, and smell by adding artificial pigment.

Twenty-four-hour emergency code break and medical information will be provided by the Data Management Center of Guang’anmen Hospital. Each subject will be allowed access to the investigator through telephone in case of emergency. In case of a severe adverse event, an administrator will unblind the patient information as an emergency and provide relevant treatment.

### Intervention

2.6

All investigators will be clinical doctors with certification in endocrinology with at least 3 years’ experience and will receive standardized training for the diagnostic interview before the start of the research. Two clinicians will diagnose the mild subclinical hypothyroidism. Participants in the intervention group will take SD orally twice a day for 12 weeks, whereas participants in the control group will take placebo orally twice a day for 12 weeks. Patient visits will be required at 0, 4, 8, and 12 weeks.

The placebo is composed of 95% starch, 5% SD, and a very small amount of bitterant. The SD and placebo (Sichuan New Green Co., Ltd., Chengdu, Sichuan, China) will be produced at a dosage of 4 g, with shelf-life of 2 years.

### Follow-up

2.7

All included participants will be re-evaluated at 6, and 12 months through phone calls or as outpatients. Participants with worsened thyroid function will receive a supply of relevant medicine and a written withdrawal schedule.

### Outcome measures

2.8

#### Primary outcomes

2.8.1

The primary endpoint is the change in Thyroid-related Quality of Life Questionnaire (ThyPRO) results from baseline to week 12, with severity rating on a scale of 0 to 100 at 0, 4, 8, and 12 weeks from the start of the treatment period.^[10,34]^

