#### Sample size

2.9.1

This study is a trial of a new therapeutic regimen of SD treatment. In a similar study conducted previously on selenium supplementation, the total sample size was 192 participants.^[35]^ Allowing for a 20% withdrawal rate, we plan to include 228 patients in this trial.

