#### Data analyses

2.9.2

Statistical Package for the Social Sciences (SPSS) version 17.0 (SPSS, Inc., Chicago, IL) software will be used for data analysis. An intention-to-treat analysis will be conducted for patients who underwent treatment at least once. Continuous data with normal distribution will be presented as mean ± standard deviation, and those without normal distribution as median (interquartile range). Statistical comparisons will be analyzed using the student *t* test, and Wilcoxon rank sum test for continuous data and *χ*^*2*^ test for categorical data. Differences between groups will be evaluated using the *χ*^*2*^ test or Wilcoxon rank sum test. All statistical tests will be 2-sided tests, and *P*-value of < .05 will be considered statistically significant.

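### The article contradicts itself on the primary endpoint: TSH in the Abstract, change in ThyPRO in section 2.8.1

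*Protocol article*

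**What the plan says.** The Abstract (Methods and analysis) says: "The primary outcome measure is the thyroid-stimulating hormone level". The same sentence continues: "secondary outcomes will be the differences in the results of Thyroid-related Quality of Life Questionnaire, blood lipids, and Traditional Chinese Medicine Symptom Score Scale", assessed between baseline and 12 weeks.

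Section 2.8.1 (Primary outcomes) says: "The primary endpoint is the change in Thyroid-related Quality of Life Questionnaire (ThyPRO) results from baseline to week 12".

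Section 2.8.2 (Secondary outcomes) says: "The secondary endpoint is the change in TSH from baseline to week 12". It adds blood lipids and does not mention the TCM Symptom Score Scale.

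Section 2.9.2 (Data analyses) sets one rule for every comparison: "All statistical tests will be 2-sided tests", with a P-value "of < .05 will be considered statistically significant". It gives no order or split of the significance level between TSH and ThyPRO.

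**The concern.** TSH is a laboratory marker and ThyPRO is a patient-reported measure, so the two can give different answers. If SD beat placebo on one and not on the other, the Abstract and section 2.8 would support opposite conclusions about whether the trial met its primary objective. A reader with only this article could not tell which claim had been fixed in advance. If the endpoint were settled only after the data were seen, the more favourable one could be reported as primary, and the nominal 5% level would no longer describe the risk of a false claim of success.

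The missing TCM Symptom Score Scale matters less. It does not touch the primary test, but it leaves open whether that scale is a planned secondary outcome.

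**Working it through.** **Step 1: set the statements side by side.**

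| Measure | Abstract | Sections 2.8.1 and 2.8.2 |
|---|---|---|
| TSH | primary | secondary (change to week 12) |
| ThyPRO | secondary | primary (change to week 12) |
| Blood lipids | secondary | secondary |
| TCM Symptom Score Scale | secondary | not listed |

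The roles of TSH and ThyPRO are exchanged. Neither column comes from an amendment log or describes superseded text.

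**Step 2: look for anything that settles it.**
- Section 2.9.1 (Sample size) starts from an earlier selenium study in which "the total sample size was 192 participants". It names no endpoint, so it does not show which measure the trial was sized for.
- Section 2.9.2 treats all tests alike.
- The Introduction and Discussion mention symptoms and TSH together without ranking them.
- Section 2.9.3 provides training in evaluating TCM symptoms, which suggests that the TCM scale is still in use. It says nothing about the primary endpoint.

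The article does not resolve the conflict.

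**Step 3: the error rate under each reading.**

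Input from the article: two-sided 0.05 for each test (section 2.9.2). Assumptions: no true effect on either endpoint, and test statistics that are approximately normal. The correlation between the two statistics is not given, so a range is shown.

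*One fixed primary endpoint, whichever it is.* Type I error = 0.05. This reproduces the plan's own level.

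*Choice left open until results are known.* A false claim arises if either test is significant.
- Independent tests: 1 − (1 − 0.05)² = 1 − 0.9025 = 0.0975.
- Upper bound under any dependence: 0.05 + 0.05 = 0.10.
- Correlated tests: 1 − P(|Z₁| ≤ c and |Z₂| ≤ c), where Z₁ and Z₂ are bivariate standard normal with correlation ρ and c is the two-sided 5% critical value.

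| Assumed ρ | Chance of at least one false positive |
|---|---|
| 0 | 0.0975 |
| 0.3 | 0.0951 |
| 0.5 | 0.0907 |
| 0.7 | 0.0835 |
| 0.9 | 0.0704 |

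Within this model the figure falls to 0.05 only when the two statistics are perfectly correlated.

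**The case against.** The strongest reply is that this is an inconsistency in an article and not proof that the trial lacks a defined primary endpoint. The trial was registered on 20 April 2018, ahead of recruitment planned from December 2018, and it has ethics approval. A full protocol or analysis plan may also exist. Any of these could fix one endpoint. Section 2.8.1, read alone, is clear about measure and time point, so a drafting slip in the Abstract is plausible, though the article cannot show it. This part of the reply stands, and it makes the loss of error control conditional.

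The reply also rightly says that testing everything at two-sided 0.05 does not itself create a choice of endpoint. No section says that success on either measure is enough, and with one fixed primary the same rule leaves the primary test at 5%. The problem comes from the conflicting labels.

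A reader might infer three stronger things that the article does not support:
- *That the trial has no single confirmatory test and its error rate is already above 5%.* This would require that no document fixed the endpoint before results. The article shows only that its own text does not.
- *That several ThyPRO scores push the error rate higher still.* Section 2.8.1 gives a 0 to 100 rating and no number of scores to be tested. Scores from one questionnaire are also unlikely to be independent.
- *That the endpoint conflict is why the sample size cannot be tied to an endpoint.* Section 2.9.1 states no endpoint, effect size or power. That is a separate matter, and reconciling the labels would not cure it.

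None of this removes the contradiction. The article itself states both versions, so the point is not a detail left to a fuller document.

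**Conclusion.** The concern holds in this form: the Abstract and sections 2.8.1 and 2.8.2 give opposite primary endpoints, and the article offers no means of choosing between them. This must be corrected, because the primary endpoint determines the trial's confirmatory claim and a choice made after unblinding could look driven by the results.

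The size is conditional. If the choice stays open until results are known, the chance of a false claim of success is 9.75% for independent tests, 10% at most, and about 9.5% to 7.0% for assumed correlations of 0.3 to 0.9, against 5% with one fixed primary. These figures rest on no true effect on either endpoint, each tested at two-sided 0.05. The correlations are assumptions. If a document fixed before results names one endpoint and is followed, the primary test keeps its 5% level and the remaining fault is that the article contradicts itself.

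The absence of the TCM Symptom Score Scale from section 2.8.2 is a minor discrepancy in the secondary list.

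**What to change.** Before unblinding:
1. Make the Abstract and sections 2.8.1 and 2.8.2 name the same primary endpoint: one named measure or score at week 12. Take it from the version registered and ethics-approved before the trial began. A fresh choice now could itself switch the primary endpoint.
2. If the sponsor departs from that version, record and justify the change as a dated amendment made blind to results.
3. If both TSH and ThyPRO are meant to support confirmatory claims, state a fixed order: test the primary at two-sided 0.05, and test the other confirmatorily at two-sided 0.05 only if the first is significant. This holds the overall error for the pair at 5%.
4. Make the secondary lists identical in the Abstract and section 2.8.2, including the TCM Symptom Score Scale.

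The cost is a short amendment with review-board approval, which section 2.9.5 requires for any amendment, and a correction to the published article. No new data are needed.
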